**Table 7: Sample size calculations for secondary outcome: Awareness of HIV positive status**

| Control arm | Intervention arm | Number HIV+ per cluster | HIV prevalence | K    | Power |
|-------------|------------------|-------------------------|----------------|------|-------|
| 60%         | 90%              | 21                      | 3.0%           | 0.25 | 92%   |
| 60%         | 90%              | 21                      | 3.0%           | 0.3  | 82%   |
| 60%         | 80%              | 21                      | 3.0%           | 0.25 | 64%   |
| 60%         | 80%              | 21                      | 3.0%           | 0.3  | 52%   |

Sampling will continue until the target sample size is reached in each cluster. For the STI outcomes, the sample size calculations are given below:

**Table 8: Sample size calculations for STI outcomes**

| Cluster size | Clusters | Expected outcome in control arm | Power | Coefficient of variation | Maximum prevalence in intervention arm that will show an effect |
|--------------|----------|---------------------------------|-------|--------------------------|-----------------------------------------------------------------|
| 300          | 16       | 17%                             | 80%   | 0.25                     | 11%                                                             |
| 300          | 16       | 17%                             | 80%   | 0.3                      | 10%                                                             |
| 300          | 16       | 17%                             | 90%   | 0.25                     | 10%                                                             |
| 300          | 16       | 17%                             | 90%   | 0.3                      | 9%                                                              |

### ***u. 7.3 Statistical analysis***

CONSORT guidelines for cluster randomised trials will be followed. A flowchart will be created showing the number of clusters eligible, the number allocated to each arm and the number of participants per cluster in the cross-sectional survey. Cluster-level analyses will be used to adjust for between-cluster variability, as recommended for trials with fewer than 15 clusters/arm. Descriptive analysis will be used to compare the cluster-level characteristics of the two arms, with adjustment for variables that are imbalanced between arms (avoiding variables likely to be affected by the intervention) and for stratum.

All outcomes are binary. For each outcome, the risk for each cluster will be calculated, and shown by strata and arm. The mean and SD of the log risk will be used to estimate the geometric mean and associated 95%CI for each arm of the study. Linear regression of the log mean risk on strata and arm will be used to estimate the risk ratio and 95%CI. The approximate variance for the mean risks will be obtained based on the residual mean square from a 2-way ANOVA on arm and strata. A 95% CI for this will be calculated from the variance using a t-statistic.

Pre-defined sensitivity analysis will include multiple imputation to adjust for non-participation in the survey. Participants in the intervention clusters are not necessarily expected to have received the intervention personally. As a form of exploratory analysis we will assess the difference in outcomes between intervention arm participants who accessed the CHIEDZA intervention (defined as having had at least one HIV test through the CHIEDZA service), compared to control arm participants.

- **8. Ethical Considerations**

- **8.1 Collaborative partnerships**

Community representatives have been involved in the design of the intervention and have engaged with the research team to shape the intervention. Formative research was conducted with several stakeholders including youth (HIV-infected and -uninfected), family members of youth, health care providers at health facilities, including those involved in HIV testing, clinical care, and counselling / outreach, CHWs, representatives or key informants from CBOs that are engaged in providing adherence support or related services and community members and other gatekeepers. The formative research is described in a separate protocol that was approved by local and international ethics committees (Protocol numbers as follows- MRCZ: MRCZ/A/2266; BRTI: AP144/2018; LSHTM: 14652).

The research teams will continue to actively engage with the study communities at various levels (e.g. with government structures, healthcare facilities at management and worker level, existing NGOs and CBOs providing community-based services and other stakeholder groups). As discussed in Section 4.3, an YAG has been established during the formative study and will provide guidance and feedback to the study team.

- **v. 8.2 Social value**

As described in Section 1, the worldwide burden of HIV infection continues to grow, with SSA being particularly affected. Young people have disproportionately poor outcomes across the HIV care cascade. If this study is able to show that the intervention is effective and cost-effective, it could contribute to meeting the ambitious UNAIDS targets which have been laid out as a means to ending the HIV epidemic, and which are currently not met in youth. The multifaceted approach of the intervention, incorporating the whole HIV care cascade as well as provision of SRH information and commodities and general health counselling offers value to youth in the community whether they are men or women, already infected with HIV or uninfected, even if the intervention ultimately does not impact upon the VL.

- **w. 8.3 Scientific validity**

Young people stand out as a group that have not benefitted from the numerous interventions to improve HIV outcomes, and studies consistently have shown that this group has lower levels of VL suppression, but also are less likely to have accessed HTC and linked to care if tested HIV-positive. This study will determine if providing community-based services that address each step of the cascade and that have been configured to try and improve access and coverage will impact on viral load among youth. Furthermore, the study addresses the broader issue of access of services by youth. It is well-recognised that young people face substantial barriers to accessing health services in facilities and health services in many countries give low priority to this age-group which has contributed to their poorer health gains compared with young children or adults over recent

decades. Therefore if community-based provision of services does result in high uptake (particularly of sensitive services such as SRH and HIV services), this may provide a model for delivery of other health services to this age-group. The study will be conducted according to the most rigorous standards of research and will provide an understanding about the process of implementing the intervention as well as the impact of such an intervention at community level. The study results will be shared throughout the study with national and international policy-makers to ensure that the findings are understood and that lessons from the study are implemented.

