If the eligible individual is not present the field team will pre-book study interview time. The survey team will visit the household for the actual interview at the pre-booked time. If the eligible individual is not available on the booked appointment time and date, another appointment will be made for a second visit. If the individual is not available after three visits, no further attempts will be made for that individual. If the household is empty, then neighbours will be asked to provide information on the composition of the household. If it is clear that there are no eligible individuals living in the household, then the household will not be revisited. If there are or may be eligible individuals living in the household, then the household will be visited a further two times. If there is more than one eligible individual in the household, then all eligible individuals in that household will be enrolled.

Eligibility criteria will be:

- Age  $\geq$  18 years (day of their 18th birthday or older) to 24 years (one day before their 25th birthday)
- Written informed consent to complete the questionnaire and provide a blood sample

A study number will be allocated to each participant and a fingerprint will be collected. The fingerprints will be compared with the fingerprints of CHIEDZA service attendees to explore 1) the proportion of control cluster survey participants who accessed the intervention (degree of contamination) and 2) proportion of intervention cluster survey participants who accessed the intervention. Sociodemographic details will be collected and data on exposure to the intervention, and on duration of residence will be collected to assess in-migration, movement between clusters and likelihood of contamination.

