## • **7. Statistical considerations and Data analysis**

### **s. 7.1 Outcomes**

All outcomes will be measured in the cross-sectional survey after 2 years of implementation.

The primary endpoint is the proportion of HIV positive participants in the survey who have virological suppression (viral load <1000 copies/ml), by arm.

The secondary outcomes are

- Proportion of HIV positive participants who are aware of their HIV status
- Proportion of those aware of their HIV positive status who are taking ART
- Proportion of those on ART who are virally suppressed

These outcomes correspond to the individual UNAIDS 90-90-90 targets, while the primary endpoint is the product of all three.

Other outcomes will be measured among all survey participants, regardless of HIV status. They are

- Proportion with knowledge of their HIV status
- Proportion with STIs
- Proportion of males circumcised
- Proportion of females using modern methods of contraception
- Proportion with good MHM (defined as using a clean menstrual management material to absorb or collect blood that can be changed in privacy as often as necessary for the duration of the menstruation period, using soap and water for washing the body as required, and having access to facilities to dispose of used menstrual management materials)
- Proportion with symptoms of common mental disorders (measured using the Shona Symptom Questionnaire-14 with a cutpoint of 9)
- Proportions who report tobacco, alcohol and substance use
- Sexual behavior (including no. of sexual partners in the past year and condom use)

ART drug resistance will be measured in samples that are virologically non-suppressed (subject to funding).

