The secondary outcomes rely on self-report of HIV-positive status and 2) ART use. In the ZIMPHIA survey, 50% of 15-24 year olds reported being HIV-positive, 83.7% of these reported using ART and of these 85.4% were virally suppressed. The first step of the HIV care cascade (HIV testing) appears to be the main step that will drive the difference in the primary outcome and the trial is powered to detect a difference in this step, including if there are higher proportions of those who report being HIV positive and a smaller difference between the control and intervention arms. The trial will not be powered to detect a difference in the second and third steps of the HIV care cascade.

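### The exploratory comparison of CHIEDZA-tested participants with all controls largely builds in a benefit on the two HIV-status outcomes and is open to self-selection on the rest

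*Combined protocol and SAP*

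**What the plan says.** Section 7.3 introduces the analysis as follows: "As a form of exploratory analysis we will assess the difference in outcomes between intervention arm participants". It then sets out the two groups: "participants who accessed the CHIEDZA intervention (defined as having had at least one HIV test through the CHIEDZA service), compared to control arm participants". It names no outcome to which the comparison is limited, no matching control subgroup and no estimand. The only adjustment described in the section is at cluster level: "with adjustment for variables that are imbalanced between arms (avoiding variables likely to be affected by the intervention) and for stratum". Nothing addresses who chooses to be tested.

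Two of the outcomes in section 7.1 concern knowledge of status. One is secondary, among people with HIV: "Proportion of HIV positive participants who are aware of their HIV status". The other is among all survey participants: "Proportion with knowledge of their HIV status". Section 7.2 adds that "The secondary outcomes rely on self-report of HIV-positive status".

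Elsewhere the protocol measures access more broadly. Section 5.1 compares survey fingerprints with those of service attendees to find, among other things, the "proportion of intervention cluster survey participants who accessed the intervention". Section 6.2 repeats this for contamination and coverage. Neither section makes an HIV test a condition of access.

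**The concern.** For the two status outcomes, exposure and outcome overlap. A participant enters the exposed group by having been tested, and an HIV-positive person with a positive CHIEDZA test has normally been told the result. The comparison group is every control, including those never tested anywhere. The same cut inside the control arm, people tested at their local clinic against all controls, would also favour the tested group, with no intervention involved.

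For viral suppression, the tested HIV-positive group consists largely of diagnosed people, while the controls include the undiagnosed. For the other outcomes, such as contraception, circumcision, menstrual hygiene and STIs, people who come for a test may differ from those who do not. Controls who would have come cannot be picked out.

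What is at stake is interpretation. Real gains among people newly diagnosed by CHIEDZA and gains created by the group definition would appear in one ratio and could not be separated.

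**Working it through.** **Reproducing the plan's figure.** The inputs from section 7.2, Table 7 are control awareness p0 = 0.60, intervention awareness p1 = 0.90 or 0.80, m = 21 HIV-positive participants per cluster, and k = 0.25 or 0.30. Section 4.2 gives 24 clusters randomised 1:1, so c = 12 per arm. Section 7.2 does not state alpha; two-sided 0.05 is assumed. The unmatched cluster formula is

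power = Φ( √[(c − 1)(p0 − p1)² / V] − 1.96 ), with V = p0(1 − p0)/m + p1(1 − p1)/m + k²(p0² + p1²).

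First row: V = 0.24/21 + 0.09/21 + 0.0625 × (0.36 + 0.81) = 0.0888. Then √(11 × 0.09/0.0888) = 3.34, and Φ(3.34 − 1.96) = 91.6%, against 92% stated. The other rows give 81.6%, 64.2% and 51.9%, against 82%, 64% and 52%. All four rows reproduce.

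**Awareness with no population effect.** Hold awareness at 60% in both arms overall, as if CHIEDZA only displaced testing done elsewhere. Let s be self-reported awareness among CHIEDZA-tested HIV-positive participants. The planned contrast then gives a ratio of s/0.60.

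This is arithmetically possible. If a share a of HIV-positive participants is tested and all of them report awareness, the untested must be at (0.60 − a)/(1 − a). That is 50% at a = 0.2, 33% at a = 0.4 and 0% at a = 0.6.

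The chance of a significant apparent benefit follows from the same formula, with 21a participants per cluster on the tested side, a from 0.2 to 0.6, k = 0.25 in controls and k from 0 to 0.25 in the tested group. For s = 0.80, a = 0.2 and k = 0.25: V = 0.24/21 + 0.16/4.2 + 0.0625 × (0.36 + 0.64) = 0.112. Then √(11 × 0.04/0.112) = 1.98, and Φ(0.02) = 0.51.

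| s (assumed) | Ratio s/0.60 | Chance of a significant benefit |
|---|---|---|
| 100% | 1.67 | 0.99 to 1.00 |
| 90% | 1.50 | 0.86 to 1.00 |
| 80% | 1.33 | 0.51 to 0.87 |
| 70% | 1.17 | 0.16 to 0.31 |
| 60% | 1.00 | 0.025 (nominal) |

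These chances are approximate, because the formula works on risk differences while section 7.3 analyses log risks. The documents give no control-arm figure for knowledge of status among all participants, so no ratio is computed there. The overlap between entry and outcome is the same.

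**Viral suppression: the sign is not fixed.** If only diagnosed people can be suppressed and later steps are unchanged, conditioning on diagnosis turns the 43% control value of section 7.2 into 43/0.60 = 71.7%, a ratio of 1/0.60 = 1.67. (The components printed beside the 43% multiply to 0.60 × 0.70 × 0.63 = 26.5%. The ratio is the same on either figure.)

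Now assume instead that 75% to 100% of the tested group is newly diagnosed, with 20% to 40% of these suppressed, and that the remainder are at 71.7%. At the low end all are new, at 20%: 0.20/0.43 = 0.47. At the high end: 0.75 × 0.40 + 0.25 × 0.717 = 0.479, and 0.479/0.43 = 1.11. The contrast could therefore fall well above or well below 1.

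**The case against.** The strongest reply is that the plan calls this exploratory, says that people in intervention clusters need not have received the intervention personally, and rests every main comparison on randomised arm. All of that stands, and it limits the consequence to how one supplementary result is read.

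A reader might infer that a spurious effect on awareness is certain. The documents do not support that. Awareness is self-reported, so non-disclosure lowers it. Section 3.2.1 advises annual retesting, so infection after a negative CHIEDZA test is possible. People newly diagnosed by CHIEDZA are truly made aware by it. The ratio of 1.67 is an upper bound, and part of any observed ratio may be real.

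A reader might also infer that every other outcome is biased, or biased upward. The suppression ranges show that the direction is open. For the remaining outcomes self-selection is a risk whose size the documents do not allow anyone to estimate. Nor do they show that this result would be given prominence after a null main result.

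Defining access by testing is not arbitrary, since section 7.2 identifies testing as the step expected to drive the primary outcome. It also does not exclude all previously diagnosed youth: section 3.2.2 requires a confirmatory test for those not registered in care. No such test is stated for those already in care, who could attend CHIEDZA and still count as not having accessed it. This supports adding a broader definition beside the present one.

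**Conclusion.** The point holds, within limits. For awareness of HIV-positive status and knowledge of HIV status, entry to the exposed group nearly coincides with the outcome, and the planned contrast largely builds in a benefit. With 60% awareness in both arms overall, the awareness ratio is 1.67, 1.50 or 1.33 at assumed self-reported awareness of 100%, 90% or 80% among CHIEDZA-tested people with HIV. It reaches 1.00 only if that figure falls to 60%. The 60% is the plan's own control value; the awareness levels in the tested group, the share tested and alpha are assumptions.

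For viral suppression and the other outcomes, the conclusion is only that restricting one side leaves the contrast open to self-selection of unknown size and sign. The primary and secondary comparisons by randomised arm are not touched. This is a change that should be made because it is nearly free and the rule misleads as written; it does not threaten the trial's main result.

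**What to change.** Amend the exploratory paragraph of section 7.3 in four respects.

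1. Exclude awareness of HIV-positive status and knowledge of HIV status from this contrast. Their comparisons by randomised arm remain.
2. For the remaining outcomes, adjust for survey-collected predictors of attendance that the intervention is unlikely to affect, such as age, sex and length of residence, naming the list before analysis.
3. Report the results as descriptive and non-causal.
4. Add a version with access defined as any CHIEDZA attendance, identified by the fingerprint match already planned in sections 5.1 and 6.2. Section 6.1.1 lets clients decline fingerprints, so the match will miss some attendees. The survey's own questions on exposure can show how many.

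A cluster-level analysis with randomised arm as instrument may be added as an option. The plan should then state the assumption that arm acts only through personal attendance, which outreach (section 3.3.1) and partner testing (section 3.2.1) strain. With about 21 HIV-positive participants per cluster, such estimates may be unstable for the HIV outcomes.

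The cost is a few lines of text, a little more analysis and the loss of two exploratory contrasts. No new data are needed.

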#### **x. 8.4 Risk-benefit assessment**

This community-based, cluster-randomized study can potentially incur risk of harm at both a community and an individual level. Likewise, study-related benefits may accrue at both an individual and a community level. The benefits and risks and how they will be addressed are discussed below.

##### **i. 8.4.1 Benefits and risks at community level**

If the intervention is effective, this will lead to increased level of viral suppression at population level and contribute to meeting the ambitious UNAIDS 90-90-90 targets to help end the HIV epidemic. This age-group has disproportionately poor outcomes compared to other age groups (e.g. 45% viral suppression in 15-24 year olds compared to 60% in older age groups). The intervention will likely have an impact on HIV incidence (although the study is not powered to detect this) as well as improved SRH. If the trial shows that the intervention is highly effective and cost-effective, efforts will be made to ensure that the control communities are among the first to benefit from this intervention.

Any community-based research project may present risks to a community. Communities may feel disempowered by having a research agenda imposed on them or they may be placed at risk of stigmatization by the publication or dissemination of research results. Large community research projects may disrupt intra-community social structures and networks that may not have been identified by the research team. We will conduct a detailed process evaluation, which will measure such harms and also have systems for monitoring and addressing social harms (see below). Communities will not be named in any publication or dissemination of results of the study. There could be an additional burden placed on already overwhelmed routine services. The intervention includes provision of ART and other services at community level and this may mitigate against this risk. The study team will work closely with government agencies and will not entice staff away from them by offering differential salary packages. Communication will be maintained with study communities for the duration of the study and a well-developed exit strategy will be planned with the input of all stakeholders and community engagement structures to ensure that there is a seamless transition from study to routine health services at the end of the study.

#### **ii. 8.4.2 Risks and benefits at individual level**

There are several benefits at individual level. All youth accessing the CHIEDZA service regardless of HIV status will be able to access SRH services and general health counselling. HTC will be available for both CHIEDZA service users as well as to all endline survey participants with defined linkage to care pathways in both cases. Knowledge of personal HIV status is the entry point to accessing care, treatment, while HIV-uninfected individuals will be able to access HIV prevention services.

Those who are identified to have STIs through testing will be treated according to National guidelines. Those identified with HIV through the CHIEDZA intervention will be offered immediate ART initiation. Several trials have shown that early treatment of HIV-infected patients has clinical benefit, and the WHO now recommends initiation of HIV treatment regardless of disease stage in all age-groups. ART reduces the incidence of TB and other infections, as well as protecting the immune system and significantly slowing HIV clinical progression. It also significantly reduces the risk of onward transmission to sexual partners, with a consequent decrease in the anxiety and psychological distress associated with HIV infection.

The risks include psychological trauma from learning one's HIV test status, and possible social harm, stigmatization or IPV related to intended or unintended disclosure of HIV status, either within or beyond the household. A red flag system will be in place to identify these risks. To minimise this, post-test counselling and support will be provided by staff trained to provide counselling according to national guidelines. Couple counselling and testing of partners will also be provided. Referral to CBOs will be made for those suffering from domestic violence. The risks of starting ART for any HIV infected individual includes side effects, the development of drug resistance if treatment adherence is sub-optimal and consequent limitation of future treatment options. Treatment will be in accordance with national guidelines. Toxicity associated with ART or cotrimoxazole prophylaxis will be monitored and treatment modified if necessary. Adherence support through CAPS groups or individual support will be provided to mitigate against this risk, with follow-up of those who miss their drug collection visits. Individuals who access HIV care and treatment will have their personal details and sensitive information collected, some of which will be entered into a research database. Collection and storage of sensitive health information carries with it the risk of unwanted disclosure if there is a breach of data security. A stringent protocol for maintaining confidentiality will be put into place (see Section 8.6). All intervention team staff will be trained on GCP as well as ongoing training and supervision on delivery of the intervention services.

The ethical concerns associated with using mystery clients as part of the process evaluation include the potential deceptiveness of this methodology. Mystery clients have been widely used to investigate provider behaviour and quality of care, and the process evaluation will employ mystery client methodologies that have been used in previous similar studies. All intervention team members will be informed that mystery client may visit the CHIEDZA sites. Consent for the mystery client visits will not be sought to avoid behaviour bias, as has been

demonstrated by health workers when they know they are being watched. Human subjects' regulations allow consent waivers if obtaining consent would threaten validity of the study, there is no participant harm, and the activities involved are standard. This holds true for this study.

The main risks associated with the endline survey are similar to risks relevant to any population-based epidemiological HIV research and primarily involve risks to privacy and confidentiality. This is addressed in Section 8.6. There are additional minor risks for the survey participants including the taking of specimens, which may include pain or bruising when blood samples are taken. Also, there is the risk that some questions addressed to participants, e.g. relating to their sexual behaviour or HIV infection status, may result in discomfort or distress. Those who are identified with common mental disorders or substance use problems will be referred for further care. All survey staff will undergo training in GCP and there will be a strong emphasis in staff training and supervision on the importance of strict confidentiality of information as well as on supportive interviewing skills. Blood collection will be carried out by fully trained staff using appropriate sterile procedures.

